##### DBT only

Mothers in the DBT arm will not receive parenting skills training and will participate in 16 weeks of DBT skills training only led by two Master’s or Ph.D. level clinical psychology trainees. Participants in the DBT Skills condition will receive training following the DBT Skills Training Manual 2nd Edition [41] through weekly, synchronous 1.5-h virtual group therapy sessions, as well as worksheets to complete weekly. Mindfulness, Emotion Regulation, Distress Tolerance, and Interpersonal Effectiveness skill domains will be covered. Participants will also be instructed to complete weekly Diary Cards to track DBT skills use each week [40].

*Mood tracking* will be completed using a brief weekly survey including questions on depression, parenting stress, positive mood, and recent stressful experiences. Participants will be provided with a weekly score for their depressive symptoms and parenting stress. Participants will track and graph these weekly scores in the program handbook provided to them by the research team.

##### SAU

Participants in the SAU condition will receive a list of local mental health and parenting resources, curated by our research team, and can access any intervention or resource they would like throughout the duration of the program.

#### Criteria for discontinuing or modifying allocated interventions {11b}

Should any participant disclose worsening symptoms (e.g., suicidal behavior) during the program, the clinical team will consider whether continued participation in the program is in the best interest of the participant. Participation in the program may also be discontinued if a participant engages in repeated violations of the terms of use regarding virtual group therapy sessions (e.g., breaking confidentiality by having other people visible in the background, leaving unexpectedly without alerting a clinical coach). Furthermore, if the clinical team notices that a participant’s clinical disposition or mental health needs change over the course of treatment, the clinical team may provide a referral to another mental health provider or clinic.

#### Strategies to improve adherence to interventions {11c}

To encourage engagement with the program, participants will be required to confirm their availability to attend weekly virtual group therapy sessions. Before starting the BRIDGE or DBT intervention, participants will attend a Zoom orientation meeting with a clinical coach. The purpose of the orientation meeting is to welcome participants to the program, explain the program components, review DBT assumptions and guidelines, assess safety and risky behaviors (e.g., suicidal or self-harm behavior, substance use), and answer questions. As some topics are not discussed in group given the potential to negatively affect other group members, the orientation meeting serves to assess the risk for drop-out, validate the importance of these safety concerns, and inform participants on how to reach out to facilitators individually on these topics (e.g., pre- or post-group check-ins, individual meetings outside of group time). As standard practice, participants in the BRIDGE and DBT conditions will be sent an email or SMS text reminder once per week for that week’s group and content. Should participants not present to their respective groups, a clinical coach will contact them at the 5-min mark to provide the Zoom link and invitation to join. Additional follow-up will occur for participants who miss the session and are non-responsive to the reminder. Contact will occur through multiple methods and with the use of validation and encouragement to support participants returning to the group. Participants will be informed that missing four sessions without being responsive to communication and efforts to return to the group will result in discontinued treatment.

To ensure adherence to the DBT Skills group protocol and assumptions during weekly therapy sessions, our team created a clinician-reported adherence measure. The measure was adapted from Harned and colleagues [44] for group therapy, with the integration of relevant resources [45, 46]. The measure was reviewed by experts in DBT (and co-authors on the current study) and refined. The resulting measure consists of 30 items rated as adherent, not adherent, or not applicable. Clinicians in both the BRIDGE and DBT groups will complete the adherence measure after each therapy session.

#### Relevant concomitant care permitted or prohibited during the trial {11d}

Participants will remain eligible for inclusion in the study if they receive concomitant care for mental health or parenting concerns; this will be documented and controlled for in the analysis as appropriate. Participants who are identified as having mental health concerns beyond depressive symptoms will be given access to a resource list of mental health and parenting supports and services which they may access during the program. Participants may continue with or begin additional clinical care (e.g., individual psychotherapy, psychiatric medications) throughout their study involvement. Additionally, participants who present with elevated suicidality or substance use either during the screening process or throughout the intervention will be offered appropriate care (e.g., monthly individual meetings with a clinician) or referred for additional clinical care.

#### Provisions for post-trial care {30}

If additional treatment is deemed necessary, a referral to another provider or clinic will be made and a list of community resources will be provided.

### Outcomes {12}

#### Primary outcomes (the specific measures utilized are described below in data collection and management)

The primary outcome of this study is mean change in depressive symptoms in mothers from pre- to post-intervention as measured by a self-report questionnaire [39]. Another primary outcome of this study is mean change in child behavioral problems from pre- to post-intervention, measured by parent-report questionnaire [47].

#### Secondary outcomes

A secondary outcome is mean change in parenting stress from pre- to post-intervention, which will be assessed using a self-report questionnaire [48]. We will also measure mean change in harsh parenting, using a self-report questionnaire [49].

#### Exploratory outcomes

Exploratory outcomes of this study include the mean change in family relationship quality from pre- to post-intervention, which will be assessed using self-report questionnaires measuring parenting qualities and strategies used by mothers, family support, and co-parent relationship quality. Additionally, mean change in maternal mental health symptoms will be assessed using self-report questionnaires measuring symptoms of various mental illnesses. Participants will also be asked to report on their recent exposure to stressful life events. Health and social service use will also be assessed at pre- and post-intervention.

In the intervention groups, we will measure participants’ engagement in program components, such as attendance to group and self-reported video watching (in the BRIDGE group).

Additional exploratory outcomes will consist of observational data of maternal sensitivity and child emotion regulation, measured by a virtual Zoom assessment with mothers and their children. Exploratory outcomes will also include co-parent mental health and parenting, and physiological indices of well-being (e.g., sleep and daily activity) collected using wearable Fitbit watches for monitoring participants’ heart rate.

### Participant timeline {13}

Week 0 (T1): Eligible consenting participants will receive a notice of enrollment via email. Exploratory outcomes will be assessed at this time point via opt-in virtual Zoom assessments. Participants will complete a 45-min baseline questionnaire, including primary, secondary, and exploratory outcomes. The T1 timepoint will be approximately 8 weeks prior to the start of the intervention.

Week 8: Participants randomized to either intervention condition will be sent an email regarding website login information. Participants will attend a clinical orientation meeting with clinical coaches.

Weeks 9–24: Participants in the BRIDGE condition will watch DBT and parenting skills training videos and complete the accompanying worksheets weekly. Participants in this condition will also complete brief weekly symptom tracking questionnaires and attend weekly virtual group therapy sessions.

Participants in the DBT condition will attend weekly virtual group therapy sessions and will complete educational worksheets. They will also complete brief weekly symptom tracking questionnaires.

Week 25 (T2): Participants will complete questionnaires assessing primary, secondary, and exploratory outcomes. Additional exploratory outcomes will be assessed via virtual Zoom assessment and co-parent questionnaire completion.

Week 25 + 6 months (follow-up): Six months post-intervention, participants will complete a 45-min follow-up questionnaire to assess prolonged changes in primary and secondary outcomes, as well as exploratory outcomes related to family relationships, maternal mental health symptoms, recent stressful experiences, and health and social services usage (Table 1).

**Table 1 Tab1:**
[figure not shown]
Standard Protocol Items: Recommendations for Interventional Trials (SPIRIT) schedule of enrolment, allocation, intervention, and assessments

### Sample size {14}

A sample size of 180 participants will be sufficient to assess clinically meaningful reductions in both maternal depressive and child MI symptoms between groups. Based on the feasibility pilot data, we assume an effect size of *d* = 1.02 in improvement on maternal depression symptoms for both intervention groups (BRIDGE and DBT Skills-Only) [36]. A sample size of *n* = 60 per group will provide very high power (> 99%) to compare intervention groups to SAU. Based on pilot data on child MI symptoms, we assume a within-group SD of 13 on the CBCL and a mean improvement of 14 points [36]. As we anticipate little to no improvement in the SAU arm, we assume an effect size of* d* = 1.08 between BRIDGE and SAU and an effect size of *d* = 0.54 between BRIDGE and DBT-Only (i.e., an effect size 50% smaller than for BRIDGE, based on meta-analyses on the benefit of dual generation programs) [27]. A sample size of *n* = 60 per group will provide very high power (> 99%) to compare BRIDGE with SAU and adequate power (75%) to compare BRIDGE with DBT Skills-only.

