## Abstract

**Background:**

Since the onset of the COVID-19 pandemic, the worldwide prevalence of maternal depression has risen sharply; it is now estimated that one quarter of mothers experience clinically significant depression symptoms. Exposure to maternal depression during early childhood increases the risk for the development of childhood mental illness (MI) in offspring, with altered parenting practices mediating the association between maternal depression and child outcomes. Dual-generation interventions, which aim to simultaneously treat parent and child mental health, show promise for improving outcomes for mothers with depression and their young children. The Building Regulation in Dual Generations (BRIDGE) program combines Dialectical Behavior Therapy (DBT) and parenting skills training to concurrently treat maternal depression and improve parenting practices. In pilot within-group studies, BRIDGE has led to large reductions in maternal depression and child MI symptoms. The aim of the current study is to evaluate the efficacy of BRIDGE in reducing maternal depression and child MI symptoms (primary outcomes) as well as parenting stress and harsh parenting (secondary outcomes).

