Two pilot studies have been conducted to evaluate BRIDGE [35, 36]. In a pre-post feasibility study, mothers with depression (*n* = 28) completed an in-person, 16-week trial of BRIDGE [36]. The intervention demonstrated good feasibility, with high retention (86% retention) and significant reductions in maternal depression (*d* = 1.02) and child MI (*d* = 1.08). In focus groups conducted at post-test, participants indicated that they were generally satisfied with the program [36]. Mothers expressed that they found the parenting skills complementary to the DBT skills, with one participant stating, “Because I understood the DBT language… it made it easier for me to understand it when we did it with children and the way it applies is just amazing.” In compliance with public health recommendations to reduce in-person contact and physical distance during the COVID-19 pandemic, a second pilot study was run to evaluate the efficacy of BRIDGE delivered via telehealth using asynchronous psychoeducational videos alongside synchronous weekly group sessions [35]. Participants (*n* = 39) showed significant reductions in child MI symptoms (*d* = 0.41), maternal depression (*d* = 1.13), and parenting stress *(d* = 0.39) from pre- to post-intervention [35]. Retention was high, with 92.3% of mothers completing the program [35]. Given these favorable results, further research comparing BRIDGE to other available programs is necessary to expand services to mothers in need.

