### Eligibility criteria {10}

#### Inclusion and exclusion criteria

Eligible participants must be caregivers with at least one 3–5-year-old child. The terms “mother” and “maternal” will be used throughout this paper to describe all participants; however, anyone who self-identifies as a mother or female primary caregiver (e.g., grandmothers raising grandchildren, gender diverse caregivers who identify as mothers) will be eligible to participate. Mothers must be above the age of 18, residing in Manitoba or BC, Canada, with elevated symptoms of depression (Patient Health Questionnaire [39] score ≥ 10) at the pre-survey that will occur prior to randomization. Eligible participants must also self-identify as being comfortable understanding, speaking, and reading English, having internet access, being available to attend telehealth groups, and being willing to complete T1 and T2 questionnaires. Mothers who report a suicide attempt in the past year or who have engaged in self-harm that required medical attention in the past 6 months will not be eligible to participate in the study, as the BRIDGE program is not intended to address these mental health needs. These mothers will be given a list of local mental health resources in their community that may be more suited to their needs. In addition, mothers who report a diagnosis of or treatment for post-traumatic stress disorder (PTSD), alcohol use disorder, substance use disorder, or psychotic disorder in the last year will be followed up with to evaluate whether the BRIDGE program would be suitable for their needs. Our priority is being as inclusive as possible across a diversity of mental health needs, while also acknowledging that for certain clients with severe symptomology and/or crisis-related needs, a group therapy program alone might not be an ethically appropriate service model (e.g., psychosis, dissociation due to PTSD, or substance dependence interfering with the ability to engage in programming). If a clinician judges that a participant will be able to participate and engage in BRIDGE and/or DBT, they will be considered eligible.

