### Interventions

#### Explanation for the choice of comparators {6b}

The SAU condition of the study is intended to account for potential changes in depressive symptoms and other outcomes over time [40]. When compared to the BRIDGE and DBT-only conditions, the SAU condition will provide insight into whether either intervention is associated with improved outcomes (e.g., reduced depressive symptoms and parenting stress). The DBT condition will provide evidence about the benefits of providing both mental health and parenting support to mothers with MI. We are interested in examining differences in child MI symptoms and parenting stress and behaviors between participants exposed to the BRIDGE versus DBT interventions.

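### The greater-than-99% power for maternal depression treats a single-arm pre-post change (d = 1.02) as the difference from services-as-usual, with no stated assumption for change in that arm

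*Protocol article*

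**What the plan says.** All references are to the protocol article.

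- **Sample size {14}** takes d = 1.02 from the feasibility pilot as "improvement on maternal depression symptoms for both intervention groups (BRIDGE and DBT Skills-Only" and moves directly to power above 99% for comparing the intervention groups with SAU, at 60 per group. It opens with the claim "A sample size of 180 participants will be sufficient to assess clinically meaningful reductions". An expectation of little or no SAU improvement does appear in this section, but in the calculation for the child outcome (CBCL).
- **Background and rationale {6a}** gives the source of 1.02: "In a pre-post feasibility study, mothers with depression", with 28 participants and one arm. The abstract agrees: "In pilot within-group studies, BRIDGE has led to large reductions in maternal depression and child MI symptoms".
- **Explanation for the choice of comparators {6b}** says the SAU arm is there to "account for potential changes in depressive symptoms and other outcomes over time".
- **Inclusion and exclusion criteria** require a PHQ-9 "score ≥ 10) at the pre-survey that will occur prior to randomization". The PHQ-9 is also the primary maternal outcome.
- **SAU** mothers receive a resource list and "can access any intervention or resource they would like throughout the duration of the program".
- **Participant timeline {13}** places T1 at week 0 and T2 at week 25.
- **Statistical methods {20a}** makes a linear model accounting for the pre-intervention score primary and tests BRIDGE against SAU and BRIDGE against DBT-only at 0.025 each.

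**The concern.** A change within one treated group contains the treatment effect and everything else that moves the score over the period: natural course, regression to the mean after selection on a high score, and other care. A between-arm difference contains only the first. The two coincide only if untreated mothers do not change, so the power statement in effect sets to zero the quantity that the SAU arm was included to measure.

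Maternal depression is a primary outcome. Any SAU improvement comes off the assumed 1.02. If the trial then found no clear difference, a reader who took the stated power at face value could treat that as strong evidence against efficacy, when the power for the true difference was much lower.

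**Working it through.** **Inputs from the protocol.** n = 60 per arm and d = 1.02 (Sample size); alpha 0.025 per comparison (Statistical methods). Sidedness is not stated, and two-sided is used here because it reproduces the plan's other power figure.

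**Inputs assumed.** The documents give no figure for SAU improvement on the PHQ-9, written s in SD units, so a range of 0.2 to 0.6 is used. They give no pre-post correlation r, so 0.4 to 0.6 is used. Total T1-to-T2 improvement in the active arms is held at 1.02.

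**Step 1: reproduce the plan.** Power is the probability that a noncentral t with 2n − 2 = 118 degrees of freedom and noncentrality d√(n/2) = d√30 exceeds 2.270.

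- d = 1.02: noncentrality 5.587, power 99.95%. The stated figure reproduces.
- d = 0.54 (BRIDGE against DBT-only, child outcome): noncentrality 2.958, power 75.3%, matching the stated 75%. At alpha 0.05 it would be 83.5%, so 0.025 is the level that fits.

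**Step 2: allow SAU to improve.** Net d = 1.02 − s. Without adjustment, net d goes into the same formula. With baseline adjustment, the residual SD shrinks by √(1 − r²), so the effective d is (1.02 − s)/√(1 − r²). The divisor is 0.917, 0.866 or 0.800 for r = 0.4, 0.5 or 0.6.

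| SAU improvement s | Net d | Unadjusted | r = 0.4 | r = 0.5 | r = 0.6 |
|---|---|---|---|---|---|
| 0.2 | 0.82 | 98.6% | >99% | >99% | >99% |
| 0.3 | 0.72 | 95.2% | 97.8% | 98.8% | >99% |
| 0.4 | 0.62 | 86.8% | 92.3% | 94.9% | 97.5% |
| 0.5 | 0.52 | 71.8% | 79.8% | 84.4% | 90.0% |
| 0.6 | 0.42 | 51.4% | 60% | 65% | 73% |

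**Step 3: break points.** Unadjusted, 99% power needs d = 0.843 and 80% needs d = 0.569.

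- Unadjusted: power drops below 99% at s = 1.02 − 0.843 = 0.18 and below 80% at s = 1.02 − 0.569 = 0.45.
- Adjusted, 99%: s = 1.02 − 0.843√(1 − r²), which is 0.25 at r = 0.4, 0.29 at r = 0.5 and 0.35 at r = 0.6.
- Adjusted, 80%: about 0.50 at r = 0.4 and 0.565 at r = 0.6.

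**Step 4: does anything else supply the premise?** The telehealth pilot's d = 1.13 is also pre-post, so it does not. The cited pilot tested BRIDGE only, so 1.02 for DBT-only is a further carry-over. The 0.025 level is assigned to BRIDGE–SAU but not to DBT–SAU, so for DBT–SAU these figures also assume that level.

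**The case against.** The strongest reply is that this is an optimistic planning assumption made in the open. The section says that it assumes the pilot value, and the article elsewhere calls the pilots within-group and pre-post. Small SAU improvement does no harm: unadjusted power is still 98.6% at 0.2 SD and at least 80% up to about 0.45 SD. The planned analysis adjusts for baseline, which recovers a good part of the loss. Additional care is open to every arm and is to be controlled for as appropriate. The Background reports that only one third of Canadian mothers with depression or anxiety receive treatment, which lends some support to a modest SAU change. The active arms also share the roughly 8-week wait before the intervention, so the 25 weeks do not work on SAU alone.

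Most of this stands and limits the size of the point. It does not supply the missing premise: a reader of the Sample size section is not told that the depression figure depends on zero SAU change.

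Three stronger readings are tempting and not supported:

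- **That the trial is underpowered for depression.** The documents give no SAU change, and power is high over much of the plausible range.
- **That entry at PHQ-9 ≥ 10 fixes a particular regression to the mean.** Any such figure needs an assumed source mean, SD and retest correlation. It also needs the selecting score to be the T1 score. The inclusion criteria place the cut-off at the pre-survey, whereas Screening and enrollment places it on the eligibility screener, with a separate pre-intervention questionnaire later. If T1 is a fresh measurement without a second cut-off, much or all of the regression could occur before T1. The documents also do not say which SD standardises 1.02, so a drop in baseline SD units cannot simply be subtracted from it.
- **That the expectation of little or no SAU improvement should be deleted.** That sentence serves the CBCL calculation, which is a different question.

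**Conclusion.** The point holds as a fault of premise, not of arithmetic. Power above 99% is correct for a true difference of 1.02 SD, but 1.02 is an uncontrolled change, and the step to a difference from SAU rests on an unstated and unsupported assumption of no SAU improvement on the PHQ-9. The unconditional figure survives SAU improvement up to about 0.18 SD unadjusted, or about 0.25 to 0.35 SD with baseline adjustment at r of 0.4 to 0.6. At 0.5 SD, power is about 72% unadjusted and 80–90% adjusted; at 0.6 SD, about 51% and 60–73%.

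These values rest on 60 analysed per arm, two-sided 0.025, active-arm improvement of 1.02, and assumed ranges for SAU improvement and r. The remedy is worth making because it is specific and cheap; it does not call the design or the analysis into question.

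**What to change.** In Sample size {14}:

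1. Label d = 1.02 as the within-group pre-post change of a single-arm pilot.
2. State the SAU change assumed on the PHQ-9 and derive the between-arm difference from it.
3. Replace the unconditional figure above 99% with power for the baseline-adjusted comparison over a range of SAU improvement (for example 0.2 to 0.6 SD) and of pre-post correlation (for example 0.4 to 0.6), both labelled as assumptions. The table above could serve.

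Leave the CBCL sentence and the enrolment target unchanged. The change rewords part of one paragraph; its only cost is a less favourable stated power.

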### Trial design {8}

A three-armed, parallel-design RCT with repeated measures will be used to evaluate the efficacy of the 16-week telehealth BRIDGE intervention for mental health outcomes in mothers and their children aged 3–5 years old (at study enrolment) compared to a DBT-only and SAU control group. Participants will be randomly allocated, using central randomization stratified based on telehealth session availability and location, in a 1:1:1 ratio to BRIDGE, DBT, or SAU. Primary (depression and child MI), secondary (parenting stress and harsh parenting), and some exploratory outcomes (i.e., maternal psychopathology symptoms, family relationship quality, service use) outcomes will be assessed during the enrolment period (pre-test, T1), after the last week of the BRIDGE and DBT interventions (post-test, T2), and at follow-up (T3). Exploratory outcomes of maternal sensitivity and child emotional reactivity will be assessed at T1 and T2. Physiological data will be collected via Fitbits starting at T1 and continuing until T2. Co-parent’s mental health and parenting will be assessed at T1, T2, and T3.

This trial was registered with ClinicalTrials.gov (NCT05959538). The Research Ethics Board 1 at the University of Manitoba, Fort Garry campus, has reviewed and approved this study.

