### Assignment of interventions: allocation

#### Sequence generation {16a}

Participants will be randomly allocated in a 1:1:1 ratio to the BRIDGE intervention, DBT-Skills intervention, or SAU. Stratified randomization will be applied based on (a) participants’ availability for virtual therapy timeslots (i.e., lunchtime or evening group) and (b) province of residence. Randomization will occur in blocks to ensure approximately equivalent group sizes.

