## Statistical methods

### Statistical methods for primary and secondary outcomes {20a}

Analyses for primary and secondary outcome variables, as well as exploratory outcome variables, will compare the changes over time between (a) the BRIDGE vs SAU groups and (b) BRIDGE vs DBT-only groups, each at *a* = 0.025 (combined type I error rate to 0.05). Linear models accounting for pre-intervention scores will be used as the primary analysis method. The persistence of effects at the 6-month follow-up will be examined using time-by-intervention interactions in a linear mixed-effects model, accounting for within-subject serial correlations and between-subject effects of the intervention and covariates. Standardized effect sizes for linear mixed models will be derived based on recommendations for linear mixed models [70, 71]. Standardized effect sizes of 0.20, 0.50, and 0.80 will be used to interpret small, medium, and large effects, respectively [70]. The research team will also investigate if there is baseline moderation by symptom severity to examine whether the BRIDGE intervention is more effective than the DBT-only or SAU interventions for participants who have higher symptom levels at pre-intervention.

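### Child-MI power rests on the in-person pilot effect (d = 1.08); the protocol's own telehealth pilot (d = 0.41) is neither used nor discussed, and would give much lower power

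*Protocol article*

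**What the plan says.** Sample size {14} sets 60 participants per arm. For child symptoms it states "we assume a within-group SD of 13 on the CBCL and a mean improvement of 14 points" and cites the first pilot. It expects almost no change under SAU, so the pilot's pre-post effect becomes a between-arm d of 1.08 against SAU. Half of this, 0.54, is taken for BRIDGE against DBT-only. The section concludes that 60 "per group will provide very high power (> 99%) to compare BRIDGE with SAU" and gives "adequate power (75%) to compare BRIDGE with DBT Skills-only".

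Background and rationale {6a} describes two pilots. The one cited in the sample-size section was an in-person pre-post study of 28 mothers, with child MI d = 1.08. In the other, "a second pilot study was run to evaluate the efficacy of BRIDGE delivered via telehealth using asynchronous psychoeducational videos alongside synchronous weekly group sessions"; it had 39 participants and gave child MI d = 0.41.

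Trial design {8} says that the trial evaluates "the efficacy of the 16-week telehealth BRIDGE intervention for mental health outcomes in mothers and their children". Study setting {9} and Intervention description {11a} confirm the format: videos watched on a website, plus weekly online groups. The analysis section {20a} tests BRIDGE against SAU and against DBT-only, each at 0.025 ("combined type I error rate to 0.05"), in linear models that account for pre-intervention scores.

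**The concern.** The protocol holds two estimates of BRIDGE's effect on child symptoms. The power statement uses the one from the format that the trial does not deliver, which is also the smaller study and the more favourable value. It does not mention the other estimate or say why it was passed over.

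Child MI is a primary outcome, and Objectives {7} predicts that BRIDGE will be better than both other arms on it. BRIDGE against DBT-only is the comparison that isolates the parenting component. If the trial is believed to have adequate power there and the result is null, readers may conclude that parenting content adds nothing for children. The trial's power may be too low to support that conclusion.

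**Working it through.** **Inputs.** n = 60 per arm, with allocation 1:1:1 (Sample size {14}, Sequence generation {16a}). Alpha is 0.025 per comparison ({20a}). Child-MI effects are 1.08 in person and 0.41 by telehealth ({6a}). The halving rule for DBT-only is taken as the plan gives it ({14}). Sidedness is not stated; two-sided is inferred in step 1.

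**Formula.** Two-sample t-test: noncentrality λ = d·√(n/2), df = 2n − 2, critical value t at 0.9875. For n = 60, √30 = 5.477, df = 118 and the critical value is 2.270.

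**Step 1: reproduce the plan.** 14/13 = 1.077, the plan's 1.08.
- d = 1.08: λ = 5.915, power above 99.9%.
- d = 0.54: λ = 2.958, power 75.3%.

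Both stated figures are recovered. At two-sided 0.05, d = 0.54 would give 83.5%, so the plan's convention is two-sided 0.025, with no dropout and no gain from baseline adjustment.

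**Step 2: change only the effect size.**
- BRIDGE vs SAU, d = 0.41: λ = 2.246, power 49.2%.
- BRIDGE vs DBT-only, d = 0.41/2 = 0.205: λ = 1.123, power 13.0%.

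**Step 3: allow for loss.** Telehealth pilot retention was 92.3%, so 60 × 0.923 ≈ 55 per arm. That figure describes programme completion and serves here only as a proxy for return of the T2 questionnaire. With n = 55, power is 45% and 12%.

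**Step 4: credit the planned baseline adjustment.** The effect in residual-SD units is d/√(1 − r²), with df = 117. The documents give no pre-post correlation r, so it is assumed (n = 60).

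| r | vs SAU, d = 0.41 | vs DBT-only, d = 0.205 | vs DBT-only, d = 0.54 |
|---|---|---|---|
| 0 (unadjusted) | 49% | 13% | 75% |
| 0.3 | 53% | 14% | 80% |
| 0.5 | 63% | 17% | 87% |
| 0.7 | 81% | 25% | 97% |

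To bring BRIDGE vs SAU back to 99% at d = 0.41, r would have to be about 0.88.

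**Step 5: smallest detectable effect.** 80% power at n = 60, unadjusted, needs d = 0.57.

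**Step 6: a middle value, for illustration only.** The n-weighted mean of the pilots is (28 × 1.08 + 39 × 0.41)/67 = 0.69. It gives 93% vs SAU and, halved to 0.345, 36% vs DBT-only.

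**Maternal depression.** The telehealth pilot effect (1.13) exceeds the 1.02 assumed, so that calculation is not weakened.

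**The case against.** The strongest reply is that 0.41 is no firmer than 1.08. It too is an uncontrolled pre-post effect. The article does not say how it was standardised or which child instrument that pilot used, so treating it as a between-arm CBCL effect is an assumption. Taken as a standardised mean change, its standard error is √(1/39 + 0.41²/78) = 0.167. That gives an approximate 95% interval of 0.08 to 0.74, over which power against SAU runs from about 4% to 96%. Format is also confounded with period: the telehealth pilot was a response to pandemic distancing, and the Background says that child symptoms rose at that time. All of this stands. It argues for showing a range; it does not justify reporting only the more favourable pilot.

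The planned analysis also adjusts for baseline, which raises power. This stands for BRIDGE vs SAU, where 49% is the unadjusted figure. It does not rescue BRIDGE vs DBT-only, which stays at 25% or below for r up to 0.7.

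Two stronger readings are tempting. One is that the figure above 99% is wrong and is really 49%. The documents do not support this: the plan's figures follow from its stated inputs, and 49% is one conditional scenario. The other is that the comparator rationale in {6b}, where SAU "is intended to account for potential changes in depressive symptoms and other outcomes over time", contradicts the assumption of almost no SAU change. It does not. That is the ordinary reason for a control arm, and the assumption is stated openly. Improvement under SAU would lower power, and worsening would raise it.

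**Conclusion.** The point holds as a fault in the choice and disclosure of an input; the arithmetic is sound. The child-MI power claims rest on the less applicable of two pilot estimates, and the section gives no reason for choosing it. On the telehealth estimate, power is about 49% against SAU and 13% against DBT-only unadjusted, 45% and 12% with 55 analysed per arm, and about 53–81% and 14–25% with baseline adjustment at r = 0.3 to 0.7 (60 per arm).

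These values assume that 0.41 is the true between-arm effect, that SAU does not change, that the plan's halving rule applies, and that tests are two-sided at 0.025. The BRIDGE vs DBT-only conclusion is the more robust one, since even the averaged pilot effect gives 36% unadjusted, against the stated 75%. For BRIDGE vs SAU the answer depends heavily on which effect is believed.

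**What to change.** Leave the sample size unchanged and rewrite the child-MI part of Sample size {14}:
- Give power for both pilots' effects (0.41 telehealth, 1.08 in person) and their halves, unadjusted and baseline-adjusted, with the assumed correlation stated.
- Say which effect is the base case and why.
- Replace the descriptions of power as very high and adequate with wording that matches those figures.
- State the smallest effect detectable with 80% power, about d = 0.57 unadjusted at 60 per arm.
- State that a non-significant CBCL result, above all for BRIDGE vs DBT-only, will not be read as no effect.

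The maternal-depression statement needs no change on this account. The cost is one paragraph and a less favourable stated power; recruitment, conduct and the analysis method are untouched.
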